# Exploring the scope of 4sb and 12a lymph node dissection for cT2-4 lower third gastric cancer: Study protocol for a prospective cohort trial

**DOI:** 10.3389/fsurg.2022.956346

**Published:** 2022-07-14

**Keywords:** 12a, lymph node dissection, lymph node metastasis, gastric cancer, 4sb

## Abstract

**Background:**

Currently, the extent of 4sb and 12a lymph node dissection is not clear and is based on the personal understanding of the surgeon. It may result in damage to the splenic artery and portal vein, leading to surgical complications. Therefore, this study aims to explore the scope of 4sb and 12a lymph node dissection in cT2-4 lower third gastric cancer.

**Methods:**

This is an ongoing prospective cohort trial. The total sample size required for the trial (March 2022 to February 2025) is approximately 524 patients. The participants are divided into the experimental (4sb first branch and 12a anterior lymphadenectomy) or control groups (traditional 4sb and 12a lymphadenectomy). Electronic data capture systems will be used to collect demographic, laboratory test, auxiliary examination, operation, postoperative condition, postoperative pathology, and follow-up data. The primary outcome is the 12a lymph node metastatic rate. Secondary outcomes include the pathology (consisting of the 4sb lymph node metastatic rate, the number of 4sb lymph nodes dissected, the number of 12a lymph nodes dissected and tumor pathological staging), a safety evaluation index (consisting of complications and mortality ≤30 days after surgery), an efficacy evaluation (consisting of operation data and postoperative recovery status), and follow-up data (consisting of 3-year or 5-year disease-free survival and overall survival).

**Discussion:**

By exploring the scope of 4sb and 12a lymph node dissection on the premise of ensuring radical cure of the tumor, the operation is simplified, the operation time is shortened, the damage of important blood vessels is reduced, the intraoperative and postoperative complications are reduced, and the patient recovers as soon as possible. Our study is a prospective exploration of the pathology, safety, efficacy, and prognosis of the new and traditional methods of 4sb and 12a lymph node dissection.

**Trial registration:**

Chinese Clinical Trial Registry, ChiCTR2200057698 (registration date: March 15, 2022).

## Introduction

Over the last few years, gastric cancer has ranked fifth in morbidity and fourth in mortality among all cancers globally (1). In 2020, the number of new cases and deaths from gastric cancer in China were 478,000 and 375,000 respectively, accounting for 43.9% and 48.6% of the global new cases and deaths from gastric cancer (2). The prognosis of gastric cancer is poor and the 5-year overall survival (OS) rate is only 35.9% in China (3). Lymph node metastasis (LNM) is the main metastasis of gastric cancer. Therefore, strict implementation of intraoperative lymphadenectomy is essential. According to the European Society of Medical Oncology (ESMO), National Cancer Comprehensive Network (NCCN), and Japanese Gastric Cancer Association (JGCA), D2 lymphadenectomy is considered as the standard treatment for gastric cancer. However, the extent of 4sb and 12a lymph node dissection (LND) is undefinable according to these guidelines (4–6), it tends to be based more on the surgeon's personal understanding and experience.

Adequate lymphadenectomy contributes to the radical cure of tumors and improves the prognosis. Concurrently, it improves the accuracy of postoperative pathological results and guides patients' postoperative treatment. However, A study has shown that excessive lymphadenectomy is associated with higher postoperative mortality (7). Therefore, lymphadenectomy should be controlled within an appropriate range. According to the guidelines (4–6), the scope of 4sb LND is along the left gastroepiploic artery (LGA), including the root, and the scope of 12a LND is along the proper hepatic artery (PHA), and needs to expose the anterior wall of the portal vein.

The advantage of the traditional lymphadenectomy is that it thoroughly cleans the regional lymph nodes (LNs). However, there are important blood vessels around the 4sb and 12a LNs, such as the splenic artery and portal vein. The risk of vascular damage is higher, the operation is difficult, and the operation time is long. Patients with advanced lower third gastric cancer have a low rate of 4sb and 12a LNM, and the prognosis is poor. Therefore, we designed a new cleaning range. We divided the 4sb LNs into two parts, namely those at the root of the LGA and the peripheral LNs of the first branch. 12a LNs were divided into two parts, namely the anterior and posterior peripheral LNs of the PHA. According to the patient's condition, we will take the 4sb LND area as the first branch LNs of the LGA, saving those at the root, and take the 12a LNs in the anterior area of the PHA, saving those in the posterior area, in some patients. The purpose is to simplify the operation, shorten the operation time, reduce the surgical complications, and speed up the recovery of the patient while obtaining the same radical cure effect. However, the efficacy and safety of this new technique is still unclear.

Since the scope of 4sb and 12a LND is not uniform nationally and internationally and there are few studies on the effectiveness and safety of different anatomical scopes, clinical study on the scope of 4sb and 12a LND is necessary. Therefore, we designed this experiment to compare the pathology, safety, efficacy, and prognosis of the new and traditional methods of 4sb and 12a lymphadenectomy to provide a new, alternative lymphadenectomy for patients with gastric cancer.

## Material and methods

### Study design

This is a single-center prospective cohort study. The study period is from March 2022 to February 2025. 524 patients will participate in the study. The participants are divided into the experimental (4sb first branch and 12a anterior lymphadenectomy) or control groups (traditional 4sb and 12a lymphadenectomy). After providing informed consent, the participants will be assigned for surgical treatment by the surgeon to either the experimental or control group at a 1:1 ratio. If the patients in the experimental group are found to have positive 4sb and 12a LNs during preoperative imaging examination or during the operation, they will be included in the control group for traditional lymphadenectomy. Figure 1 is a schematic diagram of the study process.

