### Participating surgeons

The surgeon's proficiency and experience in radical gastric cancer surgery with D2 lymphadenectomy have been found to affect the number of LNs dissected, postoperative recovery time, and postoperative complications (8). A meta-analysis has shown that if surgeons can perform 40 operations alone, they will be able to independently manage any issues encountered during the operation and ensure the operational standards and safety (8). The study medical team will be composed of two experienced surgeons and several experienced nurses, who will be responsible for performing operative and postoperative medical therapy. The two surgeons each completed at least 60 cases of laparoscopic radical gastric distal surgery with D2 lymphadenectomy.

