### Statistical analysis

The normally distributed data will be expressed as mean ± standard deviation, and independent sample t-test will be used for groups differences. The non-normally distributed data will be expressed by a median, and the Mann–Whitney U test will be used for groups differences. The count data will be described as frequency and percentage and Fisher's exact test will be used for groups differences. The survival curve will be analyzed with the use of Kaplan–Meier, and the log-rank test will be used to evaluate groups differences. The Cox proportional hazards model will be used to evaluate the hazard ratio. *P* < 0.05 is set as the significance level.

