## Conclusion

The limitations of this study are that the quality of evidence is lower than that of a randomized controlled study and there may be selection bias. However, we will build iterations of future study protocols based on the findings. In addition, we will also recruit more patients to determine more effective 4sb and 12a LND protocols and to provide ideas and evidence for lymphadenectomy in collaboration with other research centers.

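### The surgeon assigns patients to groups, but the stated tests for 12a metastasis and for survival take no covariates, so any stage imbalance enters the results directly

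*Protocol article*

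**What the plan says.** The design is declared as a cohort: "This is a single-center prospective cohort study" (Protocol article, Study design). In the same section, "the participants will be assigned for surgical treatment by the surgeon to either the experimental or control group at a 1:1 ratio". No random list, matching or rule for the first assignment is given. The Introduction gives the only stated basis for choosing the smaller operation: "According to the patient's condition, we will take the 4sb LND area as the first branch LNs of the LGA", with the 12a dissection limited to the anterior area, "saving those in the posterior area, in some patients". Study design adds that experimental patients found to have positive 4sb and 12a nodes on imaging or at operation change group: "they will be included in the control group for traditional lymphadenectomy".

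The Statistical analysis section names the t-test or Mann–Whitney U test for continuous data, Fisher's exact test for count data and Kaplan–Meier curves for survival, where "the log-rank test will be used to evaluate groups differences". A Cox model supplies the hazard ratio, with no covariates named. No stratification, regression adjustment, matching or propensity score appears in the article. The Conclusion accepts that "the quality of evidence is lower than that of a randomized controlled study and there may be selection bias".

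**The concern.** Fisher's exact test and the log-rank test answer a question about the treatment only if the two groups would have had similar outcomes under the same operation. Here a clinician who knows the patient's disease decides the group. A 1:1 ratio equalises the numbers in the groups, not their prognosis.

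The imbalance matters because it would concern the outcome itself. The Discussion reports that 12a metastasis is related to tumour location, depth of invasion and node stage, and that patients with 12a metastasis had worse recurrence-free and overall survival. A difference in stage between groups would therefore appear as a difference in the primary outcome and again in disease-free and overall survival. The article names selection bias as a limitation, but the stated tests do nothing about it. At stake is whether the 12a difference and the survival comparison can be attributed to the extent of dissection, which is the purpose of the study.

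**Working it through.** **Inputs from the documents.** Control 12a rate 9.1%, margin −7.4 points, one-sided α 0.025, power 80%, loss 10%, 262 per group (Sample size). In the cited 12a series, 11/413 were positive overall and 11/103 = 10.7% in stage III/IV lower-third disease; other studies range from 1.7% to 20% (Discussion).

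**Step 1: reproduce the plan's figure.** With equal true rates and unpooled variance, n per group = (1.96 + 0.8416)² × 2 × 0.091 × 0.909 / 0.074² = 7.849 × 0.16544 / 0.005476 = 237.1, so 238. Then 238 × 1.10 = 261.8, so 262 per group and 524 in total. The plan's figure is reproduced.

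**Step 2: size of the 12a shift (stage imbalances are assumed).** With no true effect of dissection scope, shift = (rate in advanced disease − rate in other disease) × difference in advanced-stage share.
- Strata 10.7% and 0%. The 0% is an assumption. It follows if the 103 are part of the 413, since all 11 positives then lie among the 103.
  - 10-point imbalance: 0.107 × 0.10 = 1.1 points.
  - 20-point imbalance: 0.107 × 0.20 = 2.1 points, and 2.14/7.4 = 29% of the margin.
- Strata 20% and 1.7%, borrowing the ends of the published range: 0.183 × 0.20 = 3.7 points, 49% of the margin.

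**Step 3: effect on the non-inferiority conclusion.** The margin is negative. Read as experimental minus control, a lower experimental 12a rate counts as worse. With 262 × 0.90 = 236 evaluable per group:
- No shift: SE = √(2 × 0.091 × 0.909 / 236) = 0.02648; 0.074/0.02648 − 1.96 = 0.835; power 79.8%.
- Experimental rate 7.0%: SE = √((0.091 × 0.909 + 0.070 × 0.930)/236) = 0.02503; (0.074 − 0.021)/0.02503 − 1.96 = 0.16; power about 56%.

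Under the 10.7%/0% strata, 9.1% against 7.0% corresponds to advanced-stage shares of 0.091/0.107 = 85% and 0.070/0.107 = 65%.

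Selection the other way (more advanced disease in the experimental group) works against the control of error. Suppose the true experimental rate is at the margin (1.7%) and is raised 2 points to 3.7%. At 238 per group SE = √((0.091 × 0.909 + 0.037 × 0.963)/238) = 0.0223, and (0.074 − 0.054)/0.0223 − 1.96 = −1.06. The chance of wrongly declaring non-inferiority is then 14.4% instead of 2.5%.

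**Step 4: survival.** The documents give no hazard ratio for stage. Assuming 2 to 3 and advanced-stage shares of 60% in control and 40% in experimental, the crude ratio of average hazards is (0.4 × 2 + 0.6)/(0.6 × 2 + 0.4) = 0.88 to (0.4 × 3 + 0.6)/(0.6 × 3 + 0.4) = 0.82, with no effect of surgery.

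**Step 5: what adjustment leaves untouched.** Suppose both groups start at 9.1% of 262 (23.8 positives) and a quarter of the experimental positives (5.96) move to control. The rates become 29.8/268.0 = 11.1% and 17.9/256.0 = 7.0%, a gap of 4.1 points. This is selection on the outcome itself, and pre-operative covariates cannot undo it.

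**The case against.** The strongest reply is that this is a condensed article on an openly non-randomised cohort, that it concedes selection bias, and that covariate sets usually belong in an analysis plan. That would answer a complaint that detail is missing. It does not answer this one: the article positively assigns covariate-free tests to the primary outcome and to survival, and these do not suit the allocation it describes.

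Several stronger readings are tempting but unsupported.
- **That every comparison is unadjusted.** The Cox model is not said to be univariable; it simply names no covariates.
- **That differences between surgeons confound the result.** The article says "The study medical team will be composed of two experienced surgeons and several experienced nurses", but nothing shows that the two assign patients differently. This is only a possibility, and the operating surgeon is not among the fields listed under Data collection.
- **That the bias favours the new operation.** The link to the patient's condition is made in the Introduction, and Study design gives no criterion for the first assignment. Even if less advanced cases received the limited dissection, the effects would diverge: survival would look better, while the lower 12a rate would make non-inferiority harder to show.

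The figures are also open to challenge, fairly. No imbalance is documented. The cited stratum is stage III/IV while the trial requires M0. The article does not say whether that stage is clinical or pathological. If it is pathological, 12a positivity contributes to stage, and the gradient overstates what pre-operative staging would predict.

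**Conclusion.** The point stands for the primary outcome and the log-rank comparison: assignment by the surgeon combined with covariate-free tests leaves stage imbalance uncorrected in both. For the Cox model the criticism is only that no covariates are named. The direction and size of the bias cannot be known from the article. The 2.1-point shift and the fall in power from about 80% to about 56% rest on assumed strata of 10.7% and 0%, an assumed 20-point imbalance, and the reading that a lower experimental rate is the inferior direction. They show that a moderate imbalance would matter against a 7.4-point margin; they do not predict what will happen. The sample size of 524 is not in question here.

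**What to change.** - **Primary analysis.** Pre-specify a covariate-adjusted risk difference for 12a metastasis and compare its confidence interval with the margin. Use standardisation from a logistic model, or propensity weighting where overlap is adequate.
- **Covariates.** Use pre-operative variables: cT and cN from the imaging already collected, age, sex, body mass index and concomitant disease. Add the operating surgeon if recorded. Adjust for clinical stage and not pathological stage, because pN depends on how many nodes are removed.
- **Survival.** Use the same covariates in the Cox model for disease-free and overall survival.
- **Unadjusted tests.** Keep Fisher's exact and log-rank tests as sensitivity analyses.
- **Transferred patients.** Analyse by the group first assigned, which requires that assignment to be recorded. Covariate adjustment does not repair the move of node-positive patients to control.

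The cost is extra analysis work and a few lines of text. Residual confounding will remain and should be stated with the results. Switching to random allocation during the study would be a redesign and is not asked for here.

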### Experimental group

We take the 4sb LNs at the first branch of the LGA and take the 12a LNs in the anterior area of the PHA. LNs in the two areas will be pathologically tested separately. The two groups of LNs will be separated and removed by the surgeon during the operation, rather than trimmed from the whole *ex vivo* pathological specimen.

The scope of 4sb LND is as follows: we choose to cut off the LGA at the beginning of the first branch of the LGA, and then sweep along the greater curvature to the LGA and the right gastroepiploic artery interchange (Figure 3).

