### Control group

We take the 4sb LNs at the first branch and the root of the LGA and take 12a LNs in the anterior and posterior areas of the PHA. LNs in the two areas will be pathologically tested separately. The two groups of LNs will be separated and removed by the surgeon during the operation, rather than trimmed from the whole *ex vivo* pathological specimen.

The scope of 4sb LND is as follows: we choose to cut off the LGA at the root of the LGA originating from the splenic artery, and then sweep along the greater curvature to the LGA and the right gastroepiploic artery interchange (Figure 3).

The scope of 12a LND is as follows: posterior border is the anterior side of the portal vein. The remaining borders are the same as the experimental group (Figure 4).

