### Data collection

We will use numbers instead of the name and sex of the enrolled patient to protect the privacy of the patient. Electronic data capture (EDC) system will be used to collect clinical data. The following data will be collected: (I) demographic, including sex, age, body mass index and concomitant disease; (II) perioperative laboratory test results, including those of routine blood and biochemical tests; (III) auxiliary examination results, including those of gastroscopy biopsy, endoscopic ultrasound and abdominal enhanced CT; (IV) surgical data, including operation time, blood loss, surgical method, extent of lymphadenectomy and intraoperative complications; (V) postoperative recovery data including time to get out of bed, time to pass gas, time to liquid food intake, time to semi-liquid food intake, postoperative hospital stay; and (VI) postoperative pathology, including pathological stage, the number of 4sb and 12a LNs dissected and metastasis rate (Table 1).

**Table 1 T1:** Checklist for clinical data collection and follow-up plan of enrolled patients.

	Baseline		Post-operation					Follow-up							
	Before operation	Operation	POD1	POD3	POD5	POD7	POD30	3 m	6 m	12 m	18 m	24 m	36 m	48 m	60 m
Inclusion/Exclusion criteria	×														
Informed consent	×														
Demographic information	×														
Laboratory tests	×	×	×	×	×	×		×	×	×	×	×	×	×	×
Operation information		×													
Postoperative recovery status			×	×	×	×	×								
Physical examination	×							×	×	×	×	×	×	×	×
Chest CT	×									×		×	×	×	×
Abdomen enhanced CT	×							×	×	×	×	×	×	×	×
Gastroscopy	×									×		×	×	×	×
Ultrasound gastroscope	×														
Pathology	×					×									
Complications							×								
Mortality							×	×	×	×	×	×	×	×	×
Recurrence								×	×	×	×	×	×	×	×

*“×”, the need to collect the clinical data.*

*POD, postoperative day.*

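### The node check that decides who keeps the limited dissection is prescribed only in the experimental group, so disease left behind after a negative check has no direct estimate

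*Protocol article*

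**What the plan says.** All places are in the protocol article.

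- **Study design, allocation:** "the participants will be assigned for surgical treatment by the surgeon to either the experimental or control group at a 1:1 ratio". Allocation is not random.
- **Study design, switch rule:** "If the patients in the experimental group are found to have positive 4sb and 12a LNs during preoperative imaging examination or during the operation". The stated consequence is a transfer: "they will be included in the control group for traditional lymphadenectomy". The rule is written for the experimental group only.
- **Introduction:** the posterior 12a nodes are left in place selectively, "saving those in the posterior area, in some patients", depending on the patient's condition.
- **Experimental group section, on extent:** "We take the 4sb LNs at the first branch of the LGA and take the 12a LNs in the anterior area of the PHA". The 4sb root and posterior 12a nodes stay in the patient.
- **Control group section, on extent:** "We take the 4sb LNs at the first branch and the root of the LGA and take 12a LNs in the anterior and posterior areas". Both spared areas are removed.
- **Interventions and Data collection:** every patient has preoperative enhanced CT, and its results are captured. Its stated purpose is clinical stage and tumour location.
- **Data collection, surgical items:** "surgical data, including operation time, blood loss, surgical method, extent of lymphadenectomy and intraoperative complications". No intraoperative judgement of the 4sb or 12a nodes is listed.

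**The concern.** The limited operation is kept only by patients whose 4sb and 12a nodes pass a look on imaging and at surgery. Its oncological safety therefore depends on how often metastasis sits in the spared areas despite a negative look. The Introduction and Discussion claim an equal radical effect, so this quantity bears on the trial's own aim.

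Two things follow from a check applied to one group:

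1. **No verification.** The patients with a negative check keep the nodes that would verify it. The patients whose nodes are removed have no prescribed check.
2. **Unlike groups.** Check-negative experimental patients are set against controls who were not selected in this way and who also absorb the check-positive converts. Deciding where converts are counted would not by itself supply check-negative controls as a like-for-like comparator.

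**Working it through.** **1. The plan's own figure.** Inputs from the Sample size section: control 12a rate 9.1%, margin 7.4 percentage points, one-sided alpha 0.025, power 80%, loss 10%.

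n per group = 2 × 0.091 × 0.909 × (1.960 + 0.842)² / 0.074² = 237.1, so 238. Then 238 × 1.10 = 261.8, so 262 per group and 524 in total. The stated size reproduces and this point does not affect it.

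**2. Who has what, under the text as written.**

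| Patients | Check result | Pathology of spared areas |
|---|---|---|
| Experimental, retained | negative | none (nodes left in place) |
| Experimental, converted | positive | yes |
| Assigned controls | none prescribed | yes |

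Patients who are negative on the check as a whole and have pathology of the spared areas: 0 of 524.

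**3. Possible size of the unmeasured rate (posterior 12a).** The documents give neither the share of 12a disease that is posterior nor the sensitivity of the check. Assume a posterior share f of 10%, 25% or 50%, and a sensitivity s of 30%, 50% or 70%, equal in both parts of the station.

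- 12a-positive among 262 patients: 262 × 0.091 = 23.8
- Missed posterior cases: 23.8 × f × (1 − s)
- Check-negative patients: 262 − 23.8 × s, which is 254.8, 250.1 or 245.3
- Missed rate = missed posterior cases / check-negative patients

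| f | s = 30% | s = 50% | s = 70% |
|---|---|---|---|
| 10% | 1.7/254.8 = 0.7% | 1.2/250.1 = 0.5% | 0.7/245.3 = 0.3% |
| 25% | 4.2/254.8 = 1.6% | 3.0/250.1 = 1.2% | 1.8/245.3 = 0.7% |
| 50% | 8.3/254.8 = 3.3% | 6.0/250.1 = 2.4% | 3.6/245.3 = 1.5% |

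The range is about 0.3% to 3.3%. The documents give no planning rate for the 4sb root, so no figure is offered for it.

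**4. What recording the check in controls would give.** Exact (Clopper-Pearson) limits:

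- 0 missed of 262: upper 97.5% limit = 1 − 0.025^(1/262) = 1.4%
- 3 missed of 262: 1.1% (95% CI 0.2% to 3.3%)
- With about 250 check-negative controls, the same formula gives 1 − 0.025^(1/250) = 1.5% for none missed. With 236 patients (262 less 10%), it gives 1.6%.
- Sensitivity for posterior disease: at f = 25% about 6 controls are posterior-positive, and 3 of 6 gives 50% (95% CI 12% to 88%).

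**5. Indirect route.** One could subtract the posterior rate detected in converts from the posterior rate in assigned controls. At f = 25% and s = 50%, with 236 per group, the rates are 0.091 × 0.25 = 2.275% and half of that, 1.1375%. The difference is 1.1%, with standard error √(0.02275 × 0.97725/236 + 0.011375 × 0.988625/236) = 1.19 points and 95% CI −1.2% to 3.5%. This is weak even if the groups were comparable and analysed as assigned. Surgeon allocation and the transfer of converts into control remove that basis.

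**The case against.** The strongest reply is that this is a condensed article. The data list is introduced as examples, station-level fields belong in the case report form, and the flow chart is not shown. A switch rule naturally speaks only of patients who can switch, and diagnostic accuracy is not a stated objective. Part of this stands: a control-arm check may exist in the full protocol. But the text states a rule that selects one group only, and no later analysis can recover an intraoperative judgement that was not recorded before dissection.

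Stronger readings are tempting, and the documents do not support them:

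- **That the check cannot be verified at all.** Retained experimental patients do have anterior-12a and first-branch-4sb pathology. A positive node there is a visible miss. The gap is confined to the spared areas.
- **That no outcome of the check is captured.** The extent of lymphadenectomy is recorded. In patients assigned to the experimental group it shows the result of the combined check, provided the original assignment is kept.
- **That nothing can be rebuilt.** CT is done and captured in everyone, so a blinded re-read of control scans could recover the imaging part.
- **That the missed rate can be read from the whole 12a station.** The 9.1% includes anterior nodes that both operations remove, so it overstates what could be left behind.

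The overall posterior and root rate in controls, if reported separately, would also be a rough ceiling. It is not the rate after a negative check, and it is distorted if converts are pooled in.

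**Conclusion.** The point holds in a limited form. As the article is written, no patient is both check-negative and verified in the 4sb root and posterior 12a areas, so the rate of disease left behind after a negative check has no direct estimate. Retained experimental patients are also compared with controls not selected in the same way. The irrecoverable part is the intraoperative call in controls.

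For posterior 12a the unmeasured rate could lie anywhere from about 0.3% to 3.3%. This rests on the planned 9.1%, an assumed posterior share of 10% to 50%, and an assumed sensitivity of 30% to 70% that is equal across the station. The sample size is unaffected. This is an inexpensive improvement worth making while patients are still being operated on; it does not invalidate the planned analyses.

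**What to change.** 1. In both groups, by the same written criterion and before the 4sb and 12a nodes are dissected, record a positive/negative CT call and a positive/negative intraoperative call for each station. State whether a positive check means one station or both, since the switch rule joins the two stations with an *and*.
2. In controls, report anterior and posterior 12a, and branch and root 4sb, as separate pathology results. The Control group section's sentence on separate testing repeats that of the Experimental group section, where it can only mean 4sb versus 12a, so this needs stating.
3. Report the rate of posterior-12a and 4sb-root metastasis among check-negative assigned controls, with an exact 95% CI. Keep sensitivity for spared-area disease as a secondary description because it will be very imprecise.
4. Prespecify a comparison of retained experimental patients with check-negative controls, keeping each patient's original assignment in the data.
5. For controls already operated on, a blinded re-read of stored CT can supply the imaging call only.

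Cost: four yes/no fields per patient, one extra table, and a few seconds of data entry in theatre. No operation changes and no patients are added.
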